#### Quality control of data management

Assessment forms are initially checked for completion by the home visitor. All data are directly entered into the Care4 platform and stored in their secure electronic database. Weekly quality control procedures are carried out by the research coordinator to identify specific errors and missing data. The study statistician carries out quality control routines on an as needed basis in R. All R data sets are stored on a secure server. The research coordinator communicates all data queries to home visiting staff via email or on biweekly site calls.

#### Sample size calculation and statistical analysis

As this is a pilot study, our target sample (*N =* 60) was selected on the basis of feasibility of study completion, representativeness of the target study population (includes urban and rural sites) and with the desire to provide useful information to inform a fully powered research study (e.g., inclusion/exclusion criteria, variability in responses, estimated effects). Even so, with significance set to *a =* 0.05 and power set to 80%, using our *N =* 60 and accounting for 30% attrition, we would expect to be able to detect a large effect (*d =* 0.8) on continuous outcomes and a 35% difference in retention rates between the two groups.

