## Background

Decades of research validate early childhood home visiting as an effective strategy to support families. Home visiting programs target a range of maternal and child outcomes, including promoting healthy growth and development, and reducing maternal and child behavioral and mental health disparities. In 2010, the United States Congress authorized $1.5 billion to fund the Maternal, Infant, and Early Childhood Home Visiting (MIECHV) Program across the United States (US). MIECHV was reauthorized and funded at $400 million per year for 5 years in early 2018. The Home Visiting Evidence of Effectiveness (HomVEE) review identified 21 home visiting models that meet the US Health and Human Services criteria for an evidence-based early childhood home visiting service delivery model. Of these, 19 are eligible to be used with MIECHV funds [1, 2].

Evidence-based home visiting programs being disseminated across the US struggle with retention of families. A recent report indicated only half of participating families across four home visiting models remained in the program at one year postpartum, despite these models expecting that families remain enrolled until at least 2 years postpartum [3]. Many home visiting models were designed to serve families over several years with regularly scheduled visits. While some shorter home visiting models have seen positive outcomes, little is known regarding optimal duration and dosage [4]. Moreover, the types of families being served and the diversity of issues and challenges they present suggest the need to tailor and adapt programs to better fit a wide range of needs [5]. To date, this tailoring has almost always relied solely on the judgement of an individual home visitor or, in some cases, is guided by the implementing organization without guidance from the model developer.

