## Methods/design

### Trial design

This study uses a two-arm pilot randomized Hybrid Type 3 design [14]. Four Family Spirit home visiting sites from the Inter-Tribal Council of Michigan (ITC of MI) were selected based on comparability and randomized using a 1:1 allocation to provide either Standard Family Spirit or Precision Family Spirit to their clients. Sites were matched based on annual volume of clients served and geographic similarity (i.e., urban vs. rural) (Fig. 1).

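### The power sentence overstates what 60 mothers in four randomised sites can detect: d = 0.8 has about 72% power even before clustering, and the 35-point retention figure holds only if site randomisation is ignored

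*Protocol article*

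**What the plan says.** Under Sample size calculation and statistical analysis, the article explains that the target of 60 "was selected on the basis of feasibility of study completion, representativeness of the target study population" and the wish to inform a later, fully powered study. It then adds a power claim at alpha 0.05, with "power set to 80"% and N = 60. The authors write "accounting for 30% attrition, we would expect to be able to detect a large effect", and they put its size at d = 0.8 for outcomes measured on a continuous scale. For retention, the matching claim is "a 35% difference in retention rates between the two groups". The section does not give the sidedness of the test, the base retention rate, an intracluster correlation or a design effect.

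Under Trial design, four sites "were selected based on comparability and randomized using a 1:1 allocation". The Randomization section confirms that allocation was by site, after matching. The Primary aim analysis section plans mixed models with random effects for individual and site, and mixed logistic models for dropout that account for site. Under Primary outcomes, retention is the comparison of dropouts between arms.

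**The concern.** This is the only power statement in the document, and it describes a trial of individually randomised mothers. The d = 0.8 figure also falls short of 80% power under the conventional two-sided reading of its own inputs. Key messages on feasibility presents the pilot as a way to learn whether the two approaches differ detectably and to inform the sample size of the full trial. If the stated figures are taken at face value, a null result could be read as evidence against a large effect, which this design cannot provide.

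**Working it through.** **Inputs.** From the sample size section: N = 60, alpha 0.05, power 80%, attrition 30%, d = 0.8, 35 points. From Trial design: four sites, 1:1, so two per arm. Assumed here: equal arms (30, or 21 after attrition, since 60 × 0.7 = 42), equal sites (15, or 10.5 after attrition), a two-sided test, and a site ICC of 0.01 to 0.10, because the document gives none.

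**1. Continuous outcomes, no clustering.** SE of the standardised difference = √(2/21) = 0.309. Non-central t, 40 df:
- Power for d = 0.8 is 71.6% (73.6% by the normal approximation).
- The effect detectable at 80% power is d = 0.886.
- 25 per arm gives 79.2% and 26 per arm gives 80.7%. Twenty-six per arm is 52/0.7 = 74.3, so 75 enrolled.

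The stated figure does not reproduce. It would with 30 per arm, that is without attrition (86%), or with a one-sided 5% test at 21 per arm (81.7%). The sentence takes attrition off and does not state a one-sided test.

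**2. Continuous outcomes, sites randomised.** Design effect DE = 1 + (10.5 − 1) × ICC and SE = √(2 × DE/21). At 80% power the detectable d is 2.871 × SE on 40 df and 5.654 × SE on the 2 site-level df (4 sites − 2).

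| ICC | DE | SE | Detectable d, 40 df | Detectable d, 2 df |
|---|---|---|---|---|
| 0.01 | 1.095 | 0.323 | 0.93 | 1.83 |
| 0.05 | 1.475 | 0.375 | 1.08 | 2.12 |
| 0.10 | 1.950 | 0.431 | 1.24 | 2.44 |

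Even at ICC 0, a test on 2 df has 32% power for d = 0.8.

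**3. Retention, no clustering.** Dropout is the outcome, so every enrolled mother counts and n = 30 per arm. Power = Φ{[0.35 − 1.96√(2p̄(1 − p̄)/n)] / √([p₁(1 − p₁) + p₂(1 − p₂)]/n)}. For 40% v 75%: p̄ = 0.575, so Φ{(0.35 − 0.250)/0.119} = 80%. From 32.5% v 67.5% up to 60% v 95%, power runs from 79% to 92%. The 35-point figure therefore reproduces on all 60 mothers as if individually randomised. If attrition were deducted (21 per arm), the same rates give 63% to 80%.

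**4. Retention, sites randomised.** DE = 1 + (15 − 1) × ICC, with n replaced by 30/DE. Ranges cover the same base rates; the 2-df column uses non-central t with the unpooled SE.

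| ICC | DE | Effective n per arm | Power, normal test | Power, 2 df |
|---|---|---|---|---|
| 0.01 | 1.14 | 26.3 | 73% to 88% | 34% to 45% |
| 0.05 | 1.70 | 17.6 | 55% to 72% | 25% to 34% |
| 0.10 | 2.40 | 12.5 | 41% to 56% | 20% to 27% |

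**5. Precision.** The expected 95% CI half-width for a continuous outcome is 2.021 × 0.309 = 0.62 SD without clustering, and 4.303 × 0.375 = 1.61 SD at ICC 0.05 on 2 df.

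**The case against.** The best defence is that this is a pilot. N was chosen on feasibility, most analysis is called exploratory, the models already include site, and no decision rule rests on the power sentence. The Limitations section also concedes that few groups were randomised. All of that stands and limits the severity. It does not make the stated figures right, and the Limitations section treats the small number of sites as a problem of comparability, not of power.

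A second defence is that the planned models use repeated scores: Table 2 has two visits for acceptability and satisfaction and three for the working alliance. Averaging two visits correlated at 0.6, or three at 0.7, gives 81% power for d = 0.8 at 21 per arm without clustering. That is arithmetically sound, but the power statement mentions no averaging and no correlation, and it does nothing for the missing site allowance.

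Three stronger readings are tempting, and the document does not support them:
- **Both figures can only have come from a one-sided test.** Averaging repeated scores reaches about 80% for d = 0.8, and 60% v 95% at 21 per arm gives 80% two-sided, so a one-sided test cannot be inferred.
- **The retention figure is an arithmetic error caused by attrition.** It is about right for 60 individually randomised mothers. At ICC 0.01 with a normal test and favourable base rates it stays at or above 80%.
- **The 30% attrition contradicts the Background section.** The statement there, that "only half of participating families across four home visiting models remained in the program at one year postpartum", concerns retention in home visiting programmes generally. It is not offered as this study's attrition rate, and the trial excludes women who cannot take part in the full intervention or evaluation.

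**Conclusion.** The point holds as a correction to the stated figures. The d = 0.8 claim falls short on the sentence's own inputs (72% instead of 80%), assuming equal arms and a two-sided, single-score comparison. The retention claim falls short only because sites were randomised, and by how much depends on base rate, ICC and df, none of which the document gives. The main weakness is two sites per arm: on 2 site-level df neither figure comes near 80% power, even with a very small ICC. The ICC values are assumptions shown as a range. Nothing here shows that 60 mothers is the wrong number for a pilot chosen on feasibility.

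**What to change.** Replace the power sentence. Suggested content: with 21 retained per arm and no clustering, a two-sided 5% test has 80% power for d = 0.89. For an assumed site ICC of 0.01 to 0.10 this becomes 0.93 to 1.24 on individual df and 1.83 to 2.44 on 2 site-level df. For retention, all 60 mothers count, and for a lower-arm rate between 32.5% and 60% a 35-point difference has 79% to 92% power without clustering. Over ICC 0.01 to 0.10 that becomes 41% to 88% by normal test and about 20% to 45% on 2 df. Label the ICC range as an assumption, and name the sidedness and the df.

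Alternatively, drop the power claim and give the expected 95% CI half-width (about 0.62 SD without clustering, about 1.6 SD at ICC 0.05 on 2 df). In either case, say that a null result cannot exclude a large effect. The cost is one paragraph and less favourable figures; recruitment and design are unchanged.

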### Recruitment

The pilot study is recruiting *N* = 60 women who meet the inclusion and exclusion criteria below:

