### Randomization

Participating ITC of MI sites were randomized to use the Precision Family Spirit implementation strategy or Standard Family Spirit (control condition). Randomization occurred before recruitment began at the site level. The four sites were selected based on comparability of annual volume of clients served and geographic similarity (i.e., urban vs. rural). Once sites were matched, the study team flipped a coin to decide which sites would be assigned to each study arm. Participants are blind to whether they receive Standard Family Spirit or Precision Family Spirit as randomization occurs at the site-level. Thus, all participants at each site receive the same version of Family Spirit (standard or precision).

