#### Primary aim analysis

As this is a pilot study, most data analysis will be exploratory, but based on best practices in the field to analyze clinical trial data. We will conduct an “intent to treat” analysis as the primary analysis approach. Baseline demographic characteristics will be explored to examine comparability between the groups. For continuous measures, we will explore average scores and distributions at each time point. To test for effects, we will use mixed-effects regression models (MRMs) to estimate average differences between outcomes on the standard vs. precision approaches using the scores on the acceptability, participant satisfaction, and home visitor-client relationship assessments. Specifically, we will add a dichotomous indicator for participants receiving the precision approach compared to the standard approach and examine the interaction of that dichotomous indicator with the change in outcome measure. The MRMs will include random effects at the individual and site levels to account for multiple time points within an individual and clustering by site. We will also examine the differences in proportion of participants who dropped out and who received 50% dosage using mixed effects logistic regression models accounting for clustering by site. For all analyses, we will report both unadjusted and adjusted analyses (adjustment based on differences in baseline demographics between the two groups at the *p <* 0.1 level). For all qualitative data, we will use thematic analysis to analyze interview transcripts using Dedoose software [37]. As transcripts are reviewed, “memos” will be generated to document initial impressions of topics and themes. Segments of transcripts will then be assigned codes based on a priori (i.e., from the interview guide) or emergent themes (i.e., open coding) [38].

All analyses for the secondary outcomes will be done on an exploratory basis only.

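### The stated 80% power for d = 0.8 and for a 35-point retention difference holds only if clustering by site is ignored, although four sites were randomised

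*Protocol article*

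**What the plan says.** The section on sample size and statistical analysis explains that N = 60 was chosen for feasibility, representativeness and usefulness to a later trial. It then adds a power statement. With alpha and power fixed ("0.05 and power set to 80" per cent) and "accounting for 30% attrition, we would expect to be able to detect a large effect", the effects named are d = 0.8 for continuous outcomes and "a 35% difference in retention rates between the two groups". The section gives no sidedness, test, intraclass correlation, design effect, number of clusters or retention rate for either arm.

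The unit of randomisation is the site: "Randomization occurred before recruitment began at the site level". The Trial design and Randomization sections describe four sites, matched on client volume and urban or rural setting and allocated 1:1, so two per arm. The Primary aim analysis section plans mixed models with random effects for individual and site "to account for multiple time points within an individual and clustering by site", and mixed logistic models for dropout that also allow for site.

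**The concern.** The inputs of the power statement are those of an individually randomised trial of 60 mothers. The design and the planned models say otherwise: mothers at one site share an allocation, and any between-site variation enters the variance of the arm comparison. The power quoted is therefore for a different design from the one described.

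This is the only power statement in the article. The key messages on feasibility ask whether differences between the approaches would be detectable, and say that the results will inform sample size calculations for a full trial. A null pilot result could be read as evidence against effects of 0.8 SD or 35 points that the design could not reliably detect. An unclustered calculation could also be carried forward into a later cluster randomised trial.

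**Working it through.** **Inputs from the article.** N = 60, so 30 per arm; 30% attrition leaves 60 × 0.7 = 42, or 21 per arm; alpha 0.05; four sites, so 15 mothers per site, or 10.5 after attrition.

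**Assumptions.** Equal site sizes. ICC 0.01, 0.05 or 0.10, as none is given. Control retention 50%, taken from the only retention rate in the article ("only half of participating families across four home visiting models remained in the program at one year postpartum"), hence 50% versus 85%. The continuous calculation compares outcome levels between arms.

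**Step 1: reproduce d = 0.8 without clustering.** The standard error in SD units is √(2/21) = 0.309, so the noncentrality is 0.8/0.309 = 2.59 on 40 df.
- Two-sided 5%, single visit: power 72%; detectable d at 80% power 0.89. For d = 0.8, 26 per arm would be needed.
- One-sided 5%, single visit: power 82%; detectable d 0.78. This reproduces the claim.
- Two-sided, averaging k visits with correlation r multiplies the variance by (1 + (k − 1)r)/k. For r = 0.5 to 0.7 (assumed), two visits give factors 0.75 to 0.85 and power 83% to 78%; three visits give 0.67 to 0.80 and 87% to 81%.

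**Step 2: reproduce 35 points without clustering.** Retention is known for every mother, so 30 per arm is reasonable. The two-sided normal test, with pooled variance under the null, gives 84% for 50% versus 85% and 80% for 40% versus 75%. With 21 per arm, 50% versus 85% has 69% two-sided or 80% one-sided. The stated figure reproduces.

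Every calculation that reproduces the stated figures has a design effect of 1.

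**Step 3: add clustering, continuous outcomes.** Design effect DE = 1 + (10.5 − 1) × ICC; SE = √(2 × DE/21); noncentrality = 0.8/SE. The reference is t on 40 df (mothers as units) or on 4 − 2 = 2 df (sites as units), two-sided 5%. The noncentrality needed for 80% power is 0.886/0.3086 = 2.87 on 40 df. On 2 df it is about 5.65. Detectable d is that value times SE.

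| ICC | DE | SE | Power at 0.8, 40 df | Power at 0.8, 2 df | Detectable d, 40 df | Detectable d, 2 df |
|---|---|---|---|---|---|---|
| 0.01 | 1.10 | 0.323 | 68% | 30% | 0.93 | 1.83 |
| 0.05 | 1.48 | 0.375 | 55% | 24% | 1.08 | 2.12 |
| 0.10 | 1.95 | 0.431 | 44% | 20% | 1.24 | 2.44 |

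A one-sided 5% test gives 79%, 68% and 57% on 40 df, and 50%, 42% and 35% on 2 df. At ICC = 0, the 2-df test has 31.5% two-sided and 52.5% one-sided.

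**Step 4: add clustering, retention 50% versus 85%, 30 per arm.** DE = 1 + (15 − 1) × ICC = 1.14, 1.70, 2.40.
- Normal approximation with 30/DE per arm: 79%, 61%, 46%.
- On 2 df, SE = √[(0.5 × 0.5 + 0.85 × 0.15)/30 × DE] = 0.120, 0.146, 0.174, with noncentrality 0.35/SE = 2.92, 2.39, 2.01: power 37%, 28%, 22%.

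**Step 5: expected precision.** The 95% CI half-width on 2 df is 4.303 × SE = 1.39, 1.61 and 1.85 SD, or about 1.4 to 1.9 SD.

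**The case against.** The strongest case on the other side is that this is a pilot. N was set by feasibility, most analyses are described as exploratory, and no decision rule rests on the power sentence. The Limitations section also concedes that few groups were randomised. All of this lowers the weight of the point. It does not make the quoted power true for a site-randomised design, and the limitation is framed as one of comparability between arms, not of power.

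A reader might infer that d = 0.8 is an arithmetic error even before clustering. The article does not support that. A one-sided test reproduces it, and averaging the scheduled visits could also reach or approach it two-sided (Table 2 lists two visits for acceptability and satisfaction, three for the working alliance). The article specifies neither sidedness nor a single-visit test. What can be said is narrower: under the conventional two-sided single-visit test the figure does not follow, and the reader cannot tell which calculation was meant.

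A reader might also take the 2-df figures as the trial's actual power. The article names no degrees-of-freedom method, and that detail may properly sit in an analysis plan, so these are one scenario. Two further reservations stand. The calculation gives no credit for matching of sites. It also concerns levels, whereas the analysis section includes an arm-by-change interaction, from which a stable site intercept would cancel, although site-by-time variation would not. The same section also plans average differences between arms and a comparison of dropout proportions, for which the levels calculation is the relevant one.

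Finally, at ICC 0.01 without the small-cluster penalty the shortfall is slight: 79% for retention, and 79% for d = 0.8 one-sided.

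**Conclusion.** The point holds as a fault in the power statement, not in the choice of N. Both figures correspond to a design effect of 1, which contradicts the randomisation by site and the planned models. The 35-point figure is sound on its own unclustered terms; d = 0.8 is sound only under a sidedness or method that is not stated.

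The size depends on the unknown ICC and on the reference distribution. With mothers as units, two-sided power at d = 0.8 falls short modestly at ICC 0.01 and substantially at 0.05 or above. With sites as units it is far below 80% at every ICC tried, one- or two-sided. These results rest on equal sites, ICC 0.01 to 0.10, a comparison of levels and, for retention, an assumed 50% control rate. The correction is needed because the figure is wrong as written for this design, but the pilot's purpose and sample size are unaffected.

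**What to change.** Reword the power statement and leave N at 60:
- State the sidedness and the method behind d = 0.8 and 35 points, including whether repeated visits were used and which retention rates were assumed.
- Label both figures as ignoring clustering by site.
- Add detectable effects over a stated ICC range, for example d of about 0.93 to 1.24 on 40 df for ICC 0.01 to 0.10, with 1.8 to 2.4 as the 2-df scenario. Alternatively, replace the power claim with expected 95% CI half-widths (about 1.4 to 1.9 SD on 2 df).
- Say that the pilot is not powered to test arm effects.

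The cost is a less favourable stated figure. No change to design, recruitment or data collection is involved.

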#### Primary outcomes

Our primary outcomes of interest include participant acceptability, satisfaction, quality of relationship between home visitor and client, retention, and adherence. Acceptability is measured from the perspective of the participant using a 15-item scale [16] administered at study midpoint and endpoint. Satisfaction is captured through a 34-item questionnaire used in the Family Spirit trials and adapted specifically for this study and administered at midpoint (around 6 months postpartum) and endpoint. All Precision Family Spirit participants are invited to participate in a short qualitative interview to further explore acceptability and satisfaction using an 11-item interview guide. In addition, we will explore home visitor acceptability and satisfaction through focus group discussions that follow a 9-item interview guide. The quality of the relationship between home visitor and client is captured using the short version of the Working Alliance Inventory (WAI) administered to both participant and home visitor. The WAI measures three domains of the relationship: goal alignment, task alignment, and bond. Retention is measured by comparing the number of participants who drop out in each study arm. Adherence is measured by comparing the percentage of retained participants in each study arm who completed their lessons as prescribed.

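### The 30% attrition allowance is applied to the retention comparison, whose outcome is attrition, so the basis and power of the 35-point figure are unclear

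*Protocol article*

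**What the plan says.** Under Sample size calculation and statistical analysis, the Protocol article says that "our target sample (*N =* 60") was chosen mainly for feasibility. It then adds a power statement "with significance set to *a =* 0.05" and "power set to 80" per cent. One clause, "accounting for 30% attrition", precedes both results: d = 0.8 "on continuous outcomes and a 35% difference in retention rates between the two groups". The sentence gives no control retention rate and no sidedness, and it does not mention clustering.

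Under Primary outcomes: "Retention is measured by comparing the number of participants who drop out in each study arm". Under Primary aim analysis, where intent to treat is the primary approach: "We will also examine the differences in proportion of participants who dropped out". That comparison uses mixed-effects logistic regression that accounts for clustering by site.

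**The concern.** An attrition allowance removes people whose outcome will not be observed. For acceptability, satisfaction and alliance scores, a mother who leaves may have no later score, so a deduction is reasonable. For retention, leaving is the event being counted. A mother who drops out contributes a known result, and all 60 belong in the denominator. As written, the sentence uses attrition both as the outcome and as a loss of sample.

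Retention is a primary outcome and the main target of the implementation strategy (Implementation strategy: Precision Family Spirit, Table 1). The pilot is also meant to inform sample size calculations for a full trial (Key messages on feasibility). A reader should be able to tell what retention effect 60 mothers could show, and on what basis. The sentence does not allow that, and repeating its logic in the full trial would inflate that trial's sample size for retention.

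**Working it through.** **Inputs from the article.** Alpha 0.05, power 80%, N = 60, attrition 30%, stated difference 35 points, and four sites "randomized using a 1:1 allocation".

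**Assumptions.** Equal arms of 30 mothers, which become 30 × 0.70 = 21 after the deduction. Two-sided test unless noted. Control retention is varied because it is not given. The only retention rate in the article is about half at one year, for other home visiting models (Background).

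**Formula**, ignoring clustering, with p̄ = (p1 + p2)/2 and n per arm:

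power = Φ{ [ |p2 − p1| − z·√(2p̄(1 − p̄)/n) ] / √( [p1(1 − p1) + p2(1 − p2)]/n ) }

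**Step 1: can the 35 be reproduced?** Not uniquely. Two bases give it almost equally well:

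- 21 per arm, one-sided 5%, 50% versus 85%: power 79.9%.
- 30 per arm (no deduction), two-sided 5%, 40% versus 75%: power 79.9%.

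The companion figure does not settle the matter. At 21 per arm, d = 0.8 has 82% to 83% power one-sided and 72% to 74% two-sided (t and normal calculations).

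**Step 2: the basis as worded, two-sided, against all 60 mothers.** For 50% versus 85%, p̄ = 0.675.

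- n = 21: (0.35 − 1.96 × 0.1445)/0.1341 = 0.497, so power is 69%.
- n = 30: (0.35 − 1.96 × 0.1209)/0.1122 = 1.007, so power is 84%.

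The same calculation at other control rates:

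| Control vs Precision retention | Power, 21 per arm | Power, 30 per arm |
|---|---|---|
| 30% vs 65% | 63% | 79% |
| 40% vs 75% | 64% | 80% |
| 50% vs 85% | 69% | 84% |
| 60% vs 95% | 80% | 92% |

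**Step 3: smallest gain with 80% power (points).**

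| Control retention | 21 per arm | 30 per arm |
|---|---|---|
| 30% | 42.0 | 35.4 |
| 40% | 41.1 | 35.1 |
| 50% | 38.7 | 33.4 |
| 60% | 35.1 | 30.6 |
| 70% | not reached | 26.5 |

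The last entry for 21 per arm is a boundary case: 70% versus 100% gives 79.96% under this approximation, so nothing should rest on it. At 30 per arm the largest value over control rates is about 35.5 points.

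**Step 4: site clustering.** With 60/4 = 15 mothers per site, the design effect is 1 + 14 × ICC. The article gives no ICC, so these values are assumptions.

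- ICC 0.01: design effect 1.14, effective 30/1.14 = 26.3 per arm, detectable gain from 50% is 35.3 points.
- ICC 0.05: design effect 1.70, effective 30/1.70 = 17.6 per arm, detectable gain from 50% is 41.5 points.

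These use normal quantiles and so make no further allowance for having only two sites per arm.

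**The case against.** The strongest reply is that the number may be sound and only the sentence compressed. With all 60 mothers, two-sided and unclustered, 35 points has about 79% power or better at every control rate tabulated above, so it would serve as a cautious individual-level figure. That stands: it is not shown that the 35 was computed on 42 mothers. But the sentence then describes a basis that was not used, and it still needs correcting.

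A second reply is that a deduction could only make the retention figure pessimistic, that N = 60 rests on feasibility, and that most analyses are called exploratory. This also stands and limits the consequence. A third is that a condensed article may leave the control rate to the full protocol. That is fair as to omission alone. Here, though, the control rate is needed to tell which reading of a stated figure is meant.

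A reader might go further and infer that the two figures contradict each other: if Standard loses 30%, a 35-point gain would need 70 + 35 = 105% retention. The article does not support that as a finding. It never says that 30% is the Standard arm's loss. Read as the average over both arms, 30% is compatible with 52.5% versus 87.5%. At the roughly 50% retention reported for other models there is room for a 50-point gain. The 105% shows only what happens under an added premise.

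**Conclusion.** The point holds as a misapplied allowance and a figure with an unclear basis. Since dropout is the retention outcome, the 30% deduction has no place in that comparison. Taken literally and two-sided, the claimed 80% power falls short by roughly 11 to 17 percentage points when control retention is 30% to 50%. Without the deduction, and without clustering, the 35 points approximates the worst case and overstates the detectable gain if control retention is 60% or 70%. Neither basis makes any allowance for the site clustering that the planned analysis will model.

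These results assume equal arms and a normal approximation. The documents do not show that the authors made a computing error, nor that a 35-point difference is unattainable.

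**What to change.** Reword the power statement under Sample size calculation and statistical analysis in four respects:

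1. Apply the 30% loss to the continuous outcomes only.
2. State that retention is compared on all 60 enrolled mothers.
3. Replace the single difference with pairs of rates, naming the assumed control retention and the sidedness. For example: 50% versus 83–84%, 60% versus 91%, 70% versus 97%, two-sided, before site clustering.
4. Add the detectable difference over a stated range of assumed ICCs, such as the two values worked above, labelled as assumptions.

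The cost is wording only. The one downside is that the clustered figure will look less favourable than 35 points at the higher ICC. Sample size, recruitment and conduct are unaffected.
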